### Power analysis and target population

Using the Hedeker et al. approach [52], for a test of a between groups linear trend difference (comparing normal infant growth to those with RWG), equal sample sizes, 6 time points, a correlation among the repeated measures of 0.5, a compound symmetry structure, a medium effect size of one third of a standard deviation, an α of 0.05, and a power of 0.8, a total sample size of 184 participants (includes for estimated 20% attrition) is needed for Aim 1. To power for Aims 2–3, we reduced all EMG constructs (Fig. 1) into a single virtual covariate to facilitate computation. We then generated simulated data based on a mixed effect logistic regression model that included the virtual covariate, a sleep pattern variable and a GM diversity variable, each randomly drawn from a normal distribution and having six repeated measures. We fixed the effect size of the virtual covariate to be medium (Cohen’s f2 = 0.15), and varied the effect sizes of the sleep pattern variable and the GM diversity variable between medium (f2 = 0.15) and large (f2 = 0.35) as were observed in unpublished preliminary data. Figure 2 shows that 160 infants are required to achieve a power of 0.8 to detect a significant medium-sized effect at α = 0.05. Adjustment for a 20% attrition rate requires that we recruit 192 mother-infant pairs.

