Actigraphy is a standard, valid, noninvasive measure for assessing sleep and circadian rhythm patterns across the life course [72]. We will use the Micro Motionlogger actigraph (Ambulatory Monitoring Inc., Ardsley, New York) that will be analyzed using validated sleep-wake scoring algorithms for infant sleep [73] and adult sleep [74]. The infants and mothers will wear the devices for 5 continuous days and nights after each study visit [75, 76] to capture the full development of sleep-wake patterns and circadian rhythmicity across infancy and the level of synchrony with maternal sleep-wake patterns. Primary sleep variables will be averaged across the recording period and include (1) total sleep minutes, excluding awakenings from sleep onset to final sleep bout awakening per 24 h, (2) sleep efficiency or percent of actual sleep minutes divided by the time interval from sleep onset to morning awakening per 24 h, (3) the number of long awakenings (≥5 min) during the nocturnal sleep period, (4) longest continuous sleep interval, and (5) nocturnal sleep onset time after parent-reported bedtime. Circadian rest-activity rhythmicity will be derived from cosinor analysis by which a cosine curve is applied to the data with linear regression over a specified 24 h, as well as non-parametric circadian rhythm analysis (NPCRA) to account for the presence of ultradian rhythms and to improve estimates of sleep-wake rhythmicity in newborns [77, 78]. Primary sleep-wake circadian rhythm variables from cosinor analysis with a fixed 24-h cycle will be mesor (mean activity count), magnitude (difference between mesor and peak amount of activity), acrophase (clock time of peak activity), and R^2^ (variance explained by the cosine fit or how well the data fit a 24-h circadian rhythm), and primary variables from NPCRA will be L5 (clock time of lowest activity), M10 (clock time of highest activity), amplitude (difference between L5 and M10), inter-daily stability (measure of similarity between days of rest-activity pattern; values range from 0 to 1.0 with greater values indicating greater stability), and inter-daily variability (measure of fragmentation of the rest-activity patterns) [78].

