### Statistical analyses

To evaluate Aim 1, visit-to-visit changes in 24 h sleep and sleep-wake rhythmicity variables and their relationship to occurrence of RWG will be examined with a logistic TVEM. It can reveal critical periods during which changes in sleep-wake patterns accelerate/decelerate infant weight gain [114] and include other covariates with time-invariant effects. The TVEM model can be formulated as,

1$$ logit\;(RWG)={\beta}_0f(t)+{\Sigma}_v\kern0.5em {\beta}_vf(t)V+{\Sigma}_c\kern0.5em {\beta}_cC+\in $$where *f*(*t*) is a smooth function of time *t*, *V* is a set of variables with time-varying effects, *C* is a set of variables with time-invariant effects, *β*_0_, *β*_*v*_ and *β*_*c*_ are the corresponding coefficients, and *ϵ* is normally distributed random errors. We will impose no constraints on the *f*(*t*) function and the *β* coefficients except an assumption of smooth temporal progressions. To fit the model given the collected data, we will use the %TVEM SAS macro [115] and use a P-spline method to select the best-fitting model using knots (splitting points). Significance will be assessed based on the *p*-values of estimated *β* coefficients.

To evaluate Aim 2, we will apply the TVEM in model (1) with representing the alpha and beta diversity scores for each taxon. Because there are hundreds of taxa that may share dependencies, we will compute false discovery rates (FDRs) using the Benjamini–Hochberg procedure [116]. Taxa with FDR < 5% will be regarded as having significant associations. Given the hierarchical structure among taxa, we will further reduce the redundancies among significant taxa by ranking them on Akaike information criterion (AIC) values. Specifically, we will traverse the taxonomic tree (leaves to root) and compute AIC values for each clade. If a parent node has a lower AIC value than any of its child nodes, we will keep the parent node and remove the child nodes from the short-listed taxa.

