To evaluate Aim 3, exploratory analysis will apply principal component analysis to examine if the combination of GM variables and sleep-wake variables can explain a higher variance of RWG than using each class of variables independently. Confirmatory analysis will use model (1) to include the main effects and pairwise interactions between GM diversity scores and sleep-wake variables. Significant p-values and positive coefficients of interaction terms will indicate synergistic effects. However, because there are potentially many GM taxa associated with RWG, model (1) may include too many variables and trivial effects that reduce the statistical power. In this case, we will take a nested approach to test synergies among correlated variables. Specifically, combining the significant variables identified in Aims 1 and 2, we will first test pairwise correlations. We will then group significantly correlated variables using Gaussian finite mixture models [117] that automatically determine the number of clusters. If GM diversity scores and sleep-wake patterns coexist in a cluster, we will use model (1) extended with interaction terms to test synergistic effects. For the proposed exfoliomic data, we will utilize systems biology approaches to illuminate transgenomic cross-talk between host exfoliated intestinal epithelial cells [84] and the genomes of the gut microbiota [83, 118] in a longitudinal cohort.

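### Aim 3 labels its sleep-by-GM interaction tests confirmatory but names no deciding pair and does not extend the Aim 2 false discovery rate control to them

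*Protocol article*

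**What the plan says.** Under Statistical analyses, Aim 3 has two parts. A principal component analysis is called exploratory. The second part carries the other label: "Confirmatory analysis will use model (1) to include the main effects and pairwise interactions between GM diversity scores and sleep-wake variables". The decision rule follows: "Significant p-values and positive coefficients of interaction terms will indicate synergistic effects". If the model would hold too many variables, a nested route takes over. Variables significant in Aims 1 and 2 are pooled, tested for pairwise correlation and clustered. Interactions are then tested where GM and sleep variables share a cluster.

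The same section states one multiplicity rule, for Aim 2, using Benjamini-Hochberg: "Taxa with FDR < 5% will be regarded as having significant associations". Nothing comparable is stated for the Aim 3 interactions on either route.

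Under Power analysis and target population, the simulation for Aims 2 and 3 "included the virtual covariate, a sleep pattern variable and a GM diversity variable". Its result is that "160 infants are required to achieve a power of 0.8 to detect a significant medium-sized effect at α = 0.05". No interaction term is mentioned.

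Assessment of sleep lists the primary actigraphy measures: five sleep variables, four cosinor variables and five non-parametric rhythm variables, 14 in all. The Aim 3 hypothesis under Aim and design names four sleep features: duration, quality, bedtime and timing variability. The Discussion says that the study will explore whether these interactions affect RWG propensity.

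**The concern.** A confirmatory label tells the reader that a positive result has a known and limited chance of being false. Here the set of tests is open. Several sleep variables can be crossed with an unstated number of GM scores, and each interaction coefficient has its own p-value. With no deciding pair and no adjustment across the set, one chance result can be presented as support for the hypothesis that poor sleep and poor GM development together raise RWG risk beyond either alone.

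The article recognises multiplicity for Aim 2. For Aim 3 it treats many variables only as a threat to power, and its remedy is selection, with no control of error across the tests that remain. The article hopes that its findings will inform interventions and practice guidelines, so the evidential status of a synergy claim should be settled before analysis.

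**Working it through.** **Inputs from the article.** The significance level is 0.05, from the power section, with sidedness not stated. The synergy rule is a significant p-value and a positive coefficient. The primary actigraphy variables number 5 + 4 + 5 = 14. The Aim 3 hypothesis names 4 sleep features.

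**Assumptions.** The p-values are two-sided. There is one GM score, then two. All 4 features or all 14 variables enter, one variable per feature in the first case. The correlation between test statistics is 0, 0.5 or 0.8. The article gives none of these.

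**The plan's own figure.** For one test, 1 − (1 − 0.05)^1 = 0.05, so the stated level is right for a single interaction. The 160 infants come from a simulation whose figure is not shown, so that number cannot be re-derived.

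**Per-test false-synergy rate.** With no true interaction, a two-sided p below 0.05 falls on the positive side half the time: 0.05 / 2 = 0.025.

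**At least one false synergy among k independent tests:** 1 − (1 − 0.025)^k.
- k = 2: 1 − 0.975^2 = 4.9%
- k = 3: 1 − 0.975^3 = 7.3%
- k = 4: 1 − 0.975^4 = 9.6%
- k = 14: 1 − 0.975^14 = 29.8%

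Up to two pairs, the sign requirement alone keeps the chance below 5%. The excess begins at three.

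**Correlated tests.** For one GM score, with common correlation ρ, the chance is 1 − ∫ φ(u) Φ((1.96 − √ρ·u)/√(1 − ρ))^k du. For two GM scores the values were simulated, taking the correlation between two tests as the product of the sleep-side and GM-side correlations.

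| Sleep variables × GM scores | Pairs | Independent | 0.5 | 0.8 |
|---|---|---|---|---|
| 4 × 1 | 4 | 9.6% | 7.8% | 5.7% |
| 4 × 2 | 8 | 18.3% | 13.5% | 8.6% |
| 14 × 1 | 14 | 29.8% | 17% | 10% |
| 14 × 2 | 28 | 50.8% | 28.3% | 14.4% |

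**After a fix.** One pre-specified interaction returns the chance to 5% at most, or 2.5% with the sign rule. Under Benjamini-Hochberg at 5%, when no interaction is real, any rejection is false. The false discovery rate then equals the chance of at least one false rejection, so that chance is at most 5% for independent or positively dependent tests. The price shows in the threshold: a lone small p-value among 14 must reach 0.05 / 14 = 0.0036.

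**The case against.** The strongest reply is that this is a condensed article and that an analysis plan not shown may settle the adjustment. The article never says that the p-values are unadjusted, and it speaks of interaction terms in the plural, so it does not state that one term is enough. These points are fair, and they keep the finding modest. They do not remove it. The article itself applies the confirmatory label, gives the decision rule and specifies an adjustment for Aim 2, and it neither limits the Aim 3 tests nor carries that adjustment over.

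Three stronger readings are tempting, and the document does not support them.

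- *A reader might infer that false synergy is several times a stated 5%.* No error rate is stated for the synergy claim. The 0.05 is a per-test level in a power simulation. With four sleep features and one GM score the chance is 6-10%, which is not several-fold.
- *A reader might multiply 14 variables by many GM scores and quote very high rates.* Models of that size are what the article would probably send to the nested route, and it does not say that all 14 variables enter Aim 3.
- *A reader might infer that the nested route inflates error by re-using the same infants.* Screening on main effects does not by itself inflate an interaction test. A simulated check (160 infants, one time point, one sleep and one GM variable correlated 0.3, log-odds 0.5 each, no interaction; all assumed) gave a false-synergy rate of 2.6% both with and without the screen. The screen may also leave few pairs or none. What stands is that no adjustment is stated across the pairs that survive.

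**Conclusion.** The point holds in a limited form. The Aim 3 interaction analysis is labelled confirmatory and has a decision rule, but it has no deciding pair and no stated control across its tests. With one GM score, the chance of at least one false synergy is about 6-10% for the four hypothesised sleep features and about 10-30% for the 14 primary actigraphy variables (17% at correlation 0.5). Each range runs from test correlation 0.8 to independence. The chance grows with each further GM score.

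The figures rest on a two-sided p-value with the sign rule, and on assumed numbers of sleep variables and GM scores and assumed correlations. They show the order of magnitude and are not the error rate of a fully specified plan. The confirmatory label also sits badly with the Discussion, which speaks of exploring these interactions. This should be corrected before analysis. It does not call the design or the data collection into question.

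**What to change.** In the Aim 3 paragraph of Statistical analyses:

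1. Apply Benjamini-Hochberg at a false discovery rate below 5% across all sleep-by-GM interaction tests performed, including those reached through the nested route, as Aim 2 already does for taxa.
2. Reserve the confirmatory label for one interaction that the investigators pre-specify before analysis. The choice of pair is theirs. If they prefer not to name one, label the whole interaction analysis exploratory, in line with the Discussion.

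The cost is a change of wording and a stricter threshold for individual interactions, with some loss of power for each. No new data or visits are needed.

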### Aim and design

This study is designed as a five-year observational longitudinal study to investigate how 24-h sleep-wake patterns and GM influence RWG among infants in their first year. In this study, we aim to:
Investigate associations of infant sleep-wake patterns with subsequent RWG at 6 months and weight gain at 12 months using Time-Varying Effect Models (TVEM). We hypothesized that infants with suboptimal sleep-wake patterns (e.g., short sleep duration, poorer sleep quality [e.g., sleep percent, number of long awakenings], later bedtimes, and greater sleep-wake timing variability) will be more likely to experience RWG at 6 months and have greater total weight gain at 12 months than infants with optimal sleep-wake patterns.Investigate associations of GM development with RWG at 6 months and weight gain at 12 months. We hypothesized that infants with lower GM diversity, decreased relative abundance of beneficial microbes (e.g., *Bifidobacteria*), and increased pathogen abundance (e.g., *Staphylococcus*) across time will be more likely to experience RWG at 6 months and have greater total weight gain at 12 months.Evaluate whether temporal interactions exist between infant sleep-wake patterns and GM development, and if these relations influence RWG. We hypothesize that (1) infants with short sleep duration, poorer sleep quality, later bedtimes, and greater sleep-wake timing variability will exhibit lower GM diversity, decreased relative abundance of beneficial microbes, and increased pathogen abundance than infants with optimal sleep-wake patterns; and (2) infant sleep-wake patterns and GM development will have a synergistic effect on RWG, with suboptimal development of both factors increasing risk for RWG compared to either factor independently.

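### Aim 3 words synergy as risk with both factors against either alone, but its confirmatory rule recognises synergy only as joint odds above the product of the separate odds

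*Protocol article*

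**What the plan says.** Under *Aim and design*, the second hypothesis of Aim 3 predicts, for poor sleep and poor GM together, "a synergistic effect on RWG, with suboptimal development of both factors increasing risk for RWG compared to either factor independently". It names synergy and then explains it as a comparison of risks.

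Under *Statistical analyses*, the Aim 1 model (model 1) "will be examined with a logistic TVEM". For Aim 3, "Confirmatory analysis will use model (1) to include the main effects and pairwise interactions between GM diversity scores and sleep-wake variables". The decision rule follows: "Significant p-values and positive coefficients of interaction terms will indicate synergistic effects".

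The only stated comparison of the two classes of variables together with each class alone is a principal component analysis, asking whether the combination "can explain a higher variance of RWG than using each class of variables independently". The article labels that step exploratory.

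Under *Power analysis and target population*, the simulation model for Aims 2 and 3 "included the virtual covariate, a sleep pattern variable and a GM diversity variable". No interaction term or interaction size is described.

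**The concern.** The hypothesis and the rule use one word for different quantities. The explanation in the hypothesis, "suboptimal development of both factors increasing risk for RWG compared to either factor independently", concerns joint risk against each single-factor risk. The rule asks whether joint odds exceed the product of the two separate odds ratios. The first can be true when the second is false.

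At least three meanings are open: joint risk above either alone, joint risk above the sum of the separate excesses, and joint odds above the product. The confirmatory analysis acts only on the third. The study could therefore report no synergy while its own fitted model shows the highest RWG risk in infants with both factors suboptimal, and even a joint risk above additivity. The article intends its findings to inform preventive interventions and practice guidelines, for which the risk comparison is the practically relevant one.

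**Working it through.** **Inputs from the article.** Logistic model with main effects and product terms; synergy declared on a significant positive product term; α = 0.05 (taken as two-sided); 160 infants for Aims 2 and 3, 192 recruited for 20% attrition. The attrition step reproduces as 160 × 1.2 = 192. The 160 cannot be rebuilt, because the RWG rate, the random-effect variance and the conversion from f² to log-odds are not given.

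**Assumptions.** The article gives no RWG frequency and no interaction size, so ranges are shown. Both factors are coded so that higher means suboptimal.

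**Step 1: risks when odds exactly multiply.** With reference odds o = p00/(1 − p00) and an odds ratio of 2 for each factor:
- one factor: p10 = p01 = 2o/(1 + 2o)
- both: p11 = 4o/(1 + 4o)
- additive interaction: p11 − p10 − p01 + p00

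| Neither | One | Both | Additive interaction | Logit product term |
|---|---|---|---|---|
| 15% | 26.1% | 41.4% | +4.2 points | 0 |
| 20% | 33.3% | 50.0% | +3.3 points | 0 |
| 30% | 46.2% | 63.2% | +0.9 points | 0 |
| 33.3% | 50.0% | 66.7% | 0 | 0 |
| 40% | 57.1% | 72.7% | −1.6 points | 0 |

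Joint risk exceeds either alone in every row. It exceeds additivity only below a reference risk of one third. The coefficient that the rule tests is zero throughout.

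**Step 2: how often the rule fires.** Logistic data were simulated with two main effects and a product term, 1,000 to 2,000 data sets per setting. The rule was product-term z > 1.96. Main-effect odds ratios ran from 1.5 to 3, with a reference risk of 25% (or the risks shown) and binary or normal exposures. N = 160 is one outcome per infant. N = 960 treats six visits per infant as independent, which is an upper bound on information.

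| True state | N = 160 | N = 960 |
|---|---|---|
| Odds multiply (interaction OR 1) | 2.2–3.2% | 1.8–3.0% |
| Risks exactly additive, 20/35/35/50% (interaction OR 0.86) | 1.3% | 0.6% |
| Interaction OR 2, binary exposures | 13–18% | 66–71% |
| Interaction OR 2, normal exposures | 60–88% | close to 100% |
| Interaction OR 3, normal exposures | 91–99% | close to 100% |

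In the first two rows the hypothesis as explained is true, yet the rule is negative in about 97% to 99% of studies at either sample size. In the last three it gains power with N, as it should.

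**Step 3: what risk-scale contrasts add.** Here n = 153 (192 × 0.8 = 153.6), intercept −1.2, normal risk-coded factors, and contrasts at ±1 SD from the model that includes the product term.
- *No logit interaction.* The test that both exceeds each alone succeeds in about 59% of studies at log-OR 0.7 per SD and 29% at 0.5.
- *True interaction.* With main-effect and interaction log-OR both 0.7, the additive interaction is detected in about 97% against about 75% for the product term. With both at 0.5, the figures are about 79% against 56%.
- *Antagonism.* With main effects of 0.7 and an interaction of −0.4, the both-versus-each contrast succeeds in only about 9%.

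A check run gave the same picture within simulation error. It also showed the limit of the additive measure: with log-OR 0.7 and no logit interaction, the true risks at ±1 SD are 6.9%, 23.1% and 55.0%. The excess is 55.0 − 2 × 23.1 + 6.9 = 15.7 points, and it is detected in only about 20% of studies.

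**The case against.** The hypothesis does say synergistic, and a product term is a recognised test of synergy on the scale of the model. Read that way, the rule fits the word, and the rest of the sentence merely elaborates it. Firing in 2% to 3% of studies when the interaction is zero is the upper-tail error of a correctly sized test (nominal 2.5%), not a loss of power. The main effects come from the same model, so a null product term does not hide that both factors raise risk. The additive excess depends on an assumed RWG frequency and turns negative above one third. Finally, a condensed article may leave predicted risks and intervals to an analysis plan that is not shown.

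Most of this stands, and it limits the point. A reader might infer that the rule misses the hypothesised effect almost every time, or that it tests something unrelated to synergy. The documents support neither: the negative results of about 97% are conditional on odds that merely multiply, and with a true interaction OR of 2 to 3 and normal exposures the rule succeeds in 60% to 99% at N = 160. A reader might also propose two significant main effects as the substitute test. That would not do, because it still succeeds in 70% to 83% of simulated studies under the antagonistic interaction above.

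The objection does not remove the mismatch itself. The article fixes both the risk-worded hypothesis and the only confirmatory criterion, and one can be true while the other is null. The absence of post-estimation detail is not the complaint.

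**Conclusion.** The point holds as a mismatch between the hypothesis and its decision rule, and should be corrected before analysis. When the two factors' odds multiply, joint RWG risk exceeds either alone. With odds ratios of 2 and a reference risk below about one third, it also exceeds additivity, by 0.9 to 4.2 points at reference risks of 30% down to 15%. The rule then stays negative in about 97% of studies.

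This rests on assumed RWG frequencies and odds ratios, independent risk-coded factors, and one outcome per infant in place of the full time-varying model. It does not establish a general miss rate, and it does not make the product term an invalid test of more-than-multiplicative odds.

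**What to change.** Keep the product term, and describe a positive result as *more than multiplicative* on the odds scale. From the same fitted model, with sleep and GM variables both coded so that higher means suboptimal, report:

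1. predicted RWG risk for neither, sleep only, GM only and both suboptimal (for example at ±1 SD);
2. the contrasts of both against each factor alone;
3. the additive interaction p11 − p10 − p01 + p00, with a bootstrap interval that resamples infants.

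State that the conclusion on the second Aim 3 hypothesis rests on these risk-scale quantities, and that a null product term alone will not be reported as absence of synergy. Because joint risk above either alone does not by itself show interaction, items 2 and 3 should be read together.

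The cost is wording and post-estimation work, with no new data. There will be two interaction measures that may disagree, and risk-scale results will depend on the RWG frequency, which the article does not give.

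### The Aim 3 rule that a significant positive interaction means synergy is wrong for pairs whose two variables run in opposite risk directions, such as gut microbiota diversity with number of long awakenings

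*Protocol article*

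**What the plan says.** Under Statistical analyses, the confirmatory step for Aim 3 extends model (1), the logistic time-varying effect model, with "main effects and pairwise interactions between GM diversity scores and sleep-wake variables". One decision rule covers all these terms: "Significant p-values and positive coefficients of interaction terms will indicate synergistic effects". No condition on how the variables are coded accompanies it.

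Under Aim and design, the second Aim 3 hypothesis says what synergy is to mean: "infant sleep-wake patterns and GM development will have a synergistic effect on RWG, with suboptimal development of both factors increasing risk for RWG". The same section gives the risk directions. For GM, the Aim 2 hypothesis expects rapid weight gain (RWG) in "infants with lower GM diversity". For sleep, the suboptimal states are named in the first Aim 3 hypothesis: "infants with short sleep duration, poorer sleep quality, later bedtimes, and greater sleep-wake timing variability will exhibit lower GM diversity".

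The section Assessment of sleep lists the actigraphy variables as they will be measured. In some a larger value is the favourable state: total sleep minutes, sleep efficiency, longest sleep interval and inter-daily stability. In others a larger value is the unfavourable state: number of long awakenings, later nocturnal sleep onset and inter-daily variability, which the article describes as measuring fragmentation. Nothing in the article says that variables are turned to a common direction before products are formed.

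**The concern.** The sign of a product term depends on how its two components are coded. A rule that reads synergy from a positive sign assumes that both components increase with risk or that both decrease with it. The article's own variables break that assumption for some pairs, because a diversity score falls as risk rises while awakenings, late onset and fragmentation rise with it.

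This is the confirmatory criterion for the second Aim 3 hypothesis. Applied literally to a mixed pair, it errs both ways: the hypothesised effect cannot be recognised, and its opposite would be reported as support for the hypothesis.

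**Working it through.** The plan gives no figure on this point, so there is none to reproduce. The check has three parts: directions, algebra and a numerical illustration.

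**1. Directions for pairs with a diversity score.** Inputs are the hypotheses in Aim and design and the variable list in Assessment of sleep. The diversity score (alpha diversity) is protective-coded, since lower is the risk state.

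| Sleep variable | Higher value means | Pair with diversity | Sign under true synergy |
|---|---|---|---|
| Total sleep minutes | better | same direction | positive |
| Sleep efficiency | better | same direction | positive |
| Longest sleep interval | better | same direction | positive |
| Inter-daily stability | better | same direction | positive |
| Number of long awakenings | worse | mixed | negative |
| Later sleep onset | worse | mixed | negative |
| Inter-daily variability | worse | mixed | negative |

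The entry for sleep onset is read from the hypothesis about later bedtimes. Three of these seven directional variables form a mixed pair with diversity.

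**2. Algebra.** Let S and L both be risk-coded, for example S = awakenings and L = low diversity:

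logit p = b0 + b1·S + b2·L + b3·S·L

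Synergy on the log-odds scale is b3 > 0. The measured score is G = −L. Substituting L = −G:

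logit p = b0 + b1·S − b2·G − b3·S·G

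The fitted product coefficient is exactly −b3. If both variables are reversed, the two minus signs cancel and it is +b3. Centring a variable or dividing it by a positive constant does not change the sign. If b3 varies smoothly with time, as in model (1), the reversal applies at every time point.

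A worked value, with assumed b0 = −1, b1 = b2 = 0.5 and b3 = 0.5: an infant one unit into the risk range on both variables (S = 1, L = 1) has logit −1 + 0.5 + 0.5 + 0.5 = 0.5. In the measured coding (S = 1, G = −1) the coefficients are 0.5, −0.5 and −0.5, and the logit is −1 + 0.5·(1) − 0.5·(−1) − 0.5·(1)(−1) = 0.5. The infant and the risk are the same, but the interaction coefficient is now negative.

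**3. Numerical illustration.** Assumed: standard normal, independent predictors, one record per infant, b0 = −1, b1 = b2 = 0.5, and b3 = +0.5 (synergy) or −0.5 (antagonism). From Power analysis and target population: α = 0.05 and 160 infants.

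Large-sample fit (n = 200,000, true b3 = +0.5):
- both risk-coded: +0.498
- one risk-coded, one protective-coded: −0.498
- both protective-coded: +0.498

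At n = 160, 500 simulations for each truth, share of fits:

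| Truth | Coding | Significant and positive (called synergy) | Significant and negative |
|---|---|---|---|
| Synergy | same direction | 59.2% | 0.0% |
| Synergy | mixed | 0.0% | 59.2% |
| Antagonism | same direction | 0.0% | 67.4% |
| Antagonism | mixed | 67.4% | 0.0% |

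The percentages depend on the assumed coefficients. The exchange of the two columns between codings does not.

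**The case against.** The strongest defence is that this is a journal article. It does not say that variables enter in raw units, and Aim and design speaks throughout of suboptimal against optimal states. With every variable scored towards suboptimal, the positive-sign rule is correct, and coding is a detail that a fuller document may hold. That much stands: the article does not show that raw coding is planned. It does not rescue the rule, because the article did not leave the matter open. It fixed an unconditional sign criterion, and that criterion conflicts with its own risk directions for identifiable pairs.

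It is also fair that the rule works for most of the directional sleep variables listed, four of seven when paired with diversity.

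A reader might infer more, and the documents do not support it:
- That the plan would report a mixed synergistic pair as antagonism. The article gives no meaning to a negative coefficient; read literally, such a pair is simply not called synergy.
- That half of all pairs are affected. Two of the four possible sign codings are mixed, but that is not a count of this protocol's pairs.
- That pairs involving taxa, such as those with "increased pathogen abundance", fall under the same rule. The sentence introducing the interactions names diversity scores, so abundances are less clearly covered.
- That the fallback, which tests interactions only "If GM diversity scores and sleep-wake patterns coexist in a cluster", is an error because synergy does not need correlated exposures. The fallback is conditional on the model having too many variables, gives loss of power as its reason, and openly limits itself to correlated variables. The first Aim 3 hypothesis expects sleep and GM to be associated. The choice is debatable, and nothing says that untested pairs will be reported as showing no synergy.

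**Conclusion.** Wrong as written, for mixed-direction pairs only. When a diversity score is paired with number of long awakenings, later sleep onset or inter-daily variability, the hypothesised synergy has a negative product coefficient and the rule cannot recognise it, while antagonism has a positive one and the rule would accept it as synergy. For total sleep minutes, efficiency, longest sleep interval and inter-daily stability the rule gives the right reading.

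The sign reversal rests only on the directions stated in the hypotheses and on algebra. The size of the resulting error rates rests on the assumed effects and on a static model with one record per infant, so 59.2%, 0.0% and 67.4% are illustrations and not forecasts for this study. Synergy here means departure from additivity on the log-odds scale, which is what a product term in model (1) measures. The point concerns the interpretation of Aim 3 interactions; data collection and Aims 1 and 2 are untouched.

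**What to change.** Add one or two sentences to the Aim 3 analysis:

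- Before products are formed, orient every sleep and GM variable that has a direction so that a higher value means suboptimal, that is, higher hypothesised RWG risk; then apply the positive-sign rule. Equivalently, keep the measured coding and list the expected interaction sign for each pair.
- For measures with no good or bad direction, such as beta diversity and acrophase, state that the sign rule does not apply and test the interaction two-sided without a synergy label.

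The cost is that text and a recode at analysis, with no new data or visits. It should be written down before the Aim 3 models are fitted, so that the choice of signs cannot look driven by the results.
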